#### Validation of Noldus FaceReader vs. human coders

Our question here is whether related studies in the future could safely use the Noldus FaceReader to partially replace the human coders in assessing children’s enjoyment and engagement in the Flavour Explorers tasting activity (or a similar activity). The FaceReader software has been validated against various benchmarks, e.g. [46, 47] and used to assess children’s expressions during activities (e.g. [48]), but our context offers some particular challenges. Our participants engage in a non-screen-based activity, so gaze direction is quite variable. Also, less training data is available for children, than for adults. In our context, we are only interested in how well the automated assessment of pre-post differences in ‘Enjoyment’ and ‘Engagement’ matches those of human observers, not the moment by moment analysis of the videos.

#### Validation questions

What is the mean difference, and the variability, between FaceReader and the human coders for follow-up measures of Enjoyment and Engagement, adjusted for baseline?How significant are these differences given effect sizes?

#### Independent measures

Control/intervention groupDate of birth of childSex of childPupil Premium eligibility of childSchoolSchool class

### Participant timeline {13}

The trial runs over the 2021–2022 school year. Schools nominate eligible year groups for participation. Cluster randomisation will be at the level of paired teaching class groups, within-school. For example, a school chooses year 1 to participate. Year 1 contains two classes, 1A and 1B. At random, class 1A is assigned to the control group and 1B to the experimental group. See Fig. 1. Schools can choose the timing of intervention delivery separately for each pair of classes. Therefore, different class pairs can have different intervention timings.

**Fig. 1 Fig1:**
[figure not shown]
Participant timeline and cluster randomisation

Teachers will be instructed to ensure Flavour School delivery respects class delineations, to minimise contagion. The control group receives no intervention (i.e. the standard curriculum). Pre- and post- intervention data collection is conducted for both the experimental and control groups. The control group can receive the intervention after post-intervention data collection is complete, at the school’s discretion.

### Sample size {14}

There is no perfectly comparable study upon which to base our sample size estimates, as our behavioural measures and study design are novel to the domain. Using a similar testing method in a younger age group (1–3 year olds), Dazeley and Houston-Price [31] reported that out of 4 foods (2 fruits, 2 vegetables) offered to nursery school children, the mean number of foods tried was 1.44 with a standard deviation of 1.38. To measure mean increases of 0.5 (the equivalent of 50% of children eating one more food), using the same standard deviation found by Dazeley and Houston Price, a sample size of 160 children is needed in each arm (control and intervention) to provide 90% power. We will aim to recruit 400+ children, but recruitment may be challenging due to ongoing pandemic COVID-19 conditions.

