### Willingness-to-taste (WTT)

Children are offered nine plant foods (see Additional file 1: Appendix 1 for list of foods), in a compartmentalised tray. ‘Self-reported WTT’ is simply the proportion of these that a child tastes, as indicated by the faces they draw on their My Tasting Card (see Fig. 2).

Children are instructed that nibbling and licking are included as tasting. A child who eats all of every sample therefore has the same self-reported WTT score as a child who takes tiny nibbles of all samples, though their behaviours are notably different. To finesse WTT scores such that these differences are noted, the human observers coding the video footage will also produce a ‘Gusto’ rating to summarise how enthusiastically each child tastes/eats the food samples, rating from 1 (very unenthusiastic) to 5 (very enthusiastic). These Gusto ratings will be used to weight the self-reported WTT scores (i.e. WTT = self-report WTT * Gusto). We will report both self-report WTT and WTT.

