### Behaviour patterns expected, based on pilots

We piloted the Flavour Explorers data collection scenario with over 200 children across the target age group and across three schools. During pilots of the evaluation methods (*with no intervention*), we observed variety in children’s engagement with the Flavour Explorers activity. Most children (~77%) tasted most or all samples (7–9). A large minority (~20%) of children were more cautious, tasting 1–6 items. A small minority of children (~2%) were very reluctant and tasted zero items.^3^

There were large differences in the gusto with which children tasted. Some gingerly licked or nibbled the samples, leaving most of each sample, whilst others consumed everything available. Some children were business-like, working their way through the samples with neither great reluctance nor great enthusiasm, perhaps a bit like completing any given piece of work at school. Others were quite animated, with multiple episodes of happy, fearful, disgust and surprise expressions. Disliking some samples often did not appear much of a barrier to tasting other samples. Children often found fun in disliking foods. Engaging in the activity can produce strong negative-valence facial expressions, for example when tasting sour or disliked foods.

We were concerned that children’s attention would be excessively drawn to the cameras filming them. However, in practice during piloting, such interest was mostly confined to the beginning and end of the sessions, with the Flavour Explorers activity mostly keeping the children engaged such that they appeared to forget about or ignore the cameras.

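### The 160 children per arm for 90% power assumes individually randomised children, but classes are randomised, so the 90% is not supported

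*Protocol article*

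**What the plan says.** Under Sample size {14}, the protocol article takes its planning values from an earlier study of 1–3 year olds: "Using a similar testing method in a younger age group". That study counted tastings "out of 4 foods (2 fruits, 2 vegetables) offered to nursery school children". Its result, which supplies the planning SD here, is given as follows: "the mean number of foods tried was 1.44 with a standard deviation of 1.38". The target is put this way: "To measure mean increases of 0.5 (the equivalent of 50% of children eating one more food", and the result is that "a sample size of 160 children is needed in each arm (control and intervention) to provide 90% power". The same paragraph concedes that no closely comparable study exists. It sets a recruitment aim of at least 400 children and warns that recruitment may be difficult. It gives no ICC, class size, number of classes or design effect.

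On the design, Participant timeline {13} says: "Cluster randomisation will be at the level of paired teaching class groups, within-school". Trial design {8} also calls the trial cluster-randomised. Statistical methods {20a} recognises clustering for the analysis, and describes the clusters as too few for a multi-level model.

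On the outcome, the Willingness-to-taste section says: "Children are offered nine plant foods". The score is the proportion tasted, and the WTT measure multiplies it by a Gusto rating from 1 to 5. The pilot section reports over 200 children in the target age group: "Most children (~77%) tasted most or all samples", meaning 7–9 items, with about 20% tasting 1–6 and about 2% tasting none.

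**The concern.** Children in one class share a teacher, and in this trial they also share the counterbalanced order of the food sets. If their scores are correlated, a class-randomised trial carries less information than the same number of independently randomised children. A sample size that ignores this attaches too high a power to a given number of children.

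The planning values raise a second question. They describe a younger group on a 0–4 scale, whereas this trial scores nine foods and weights the result by Gusto.

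The interpretation of a null result is at stake. A reader told that the trial had 90% power may take a non-significant difference as evidence against a useful effect.

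**Working it through.** **Inputs from the protocol.** Difference 0.5 foods, SD 1.38, power 90%, 160 per arm, aim of 400 or more in total (about 200 per arm), allocation by paired classes.

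**Inputs assumed.** Two-sided 5% significance (not stated; one-sided 5% would give 131 per arm, so two-sided is what reproduces the figure). Consenting children per class m = 20 to 25. Class-level ICC 0.01 to 0.10.

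**Step 1: reproduce the stated figure.** n per arm = 2 × (1.960 + 1.2816)² × 1.38² / 0.5² = 160.1. Power at 160 per arm is 90.0%. The protocol's arithmetic is right for independent children. There is no room in it for clustering.

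**Step 2: add the design effect.** DE = 1 + (m − 1) × ICC. Power = Φ(0.5 / (1.38 × √(2 × DE / n)) − 1.960). Example with m = 20, ICC 0.05, n = 160: DE = 1 + 19 × 0.05 = 1.95; standard error = 1.38 × √(2 × 1.95 / 160) = 0.2154; 0.5 / 0.2154 = 2.321; Φ(0.361) = 64%. The last column is 161 × DE, rounded up (160.1 rounds up to 161).

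| ICC | m | DE | Power, 160 per arm | Power, 200 per arm | n per arm for 90% |
|---|---|---|---|---|---|
| 0.01 | 20 | 1.19 | 84% | 91% | 192 |
| 0.01 | 25 | 1.24 | 83% | 90% | 200 |
| 0.02 | 20 | 1.38 | 79% | 87% | 223 |
| 0.02 | 25 | 1.48 | 76% | 85% | 239 |
| 0.05 | 20 | 1.95 | 64% | 74% | 314 |
| 0.05 | 25 | 2.20 | 59% | 69% | 355 |
| 0.10 | 20 | 2.90 | 48% | 57% | 467 |
| 0.10 | 25 | 3.40 | 42% | 50% | 548 |

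**Step 3: what the 400-child aim covers.** 200 / 161 = 1.24, so 200 per arm absorbs a design effect of about 1.24. That corresponds to an ICC of 0.24 / 19 = 0.013 with 20 per class, or 0.24 / 24 = 0.010 with 25 per class.

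**Step 4: baseline adjustment.** The analysis is to be adjusted for baseline. Multiplying DE by (1 − r²), with r an assumed baseline–follow-up correlation taken to act equally within and between classes, gives at 200 per arm:

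- r = 0.5: 93–95% at ICC 0.02, 81–85% at 0.05, 62–69% at 0.10.
- r = 0.7: 93–95% at ICC 0.05, 79–85% at 0.10.

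At 160 per arm and ICC 0.05, the figures are 71–76% (r = 0.5) and 86–90% (r = 0.7).

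**Step 5: number of clusters.** 400 children at 20 to 25 per class make 16 to 20 classes, or 8 to 10 pairs. A test based on pair differences would have 7 to 9 degrees of freedom. The normal approximation in Steps 2 to 4 makes no deduction for this.

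**Step 6: the scale of the inputs.** Scaling both inputs from four to nine foods gives a difference of 0.5 × 9/4 = 1.125 and an SD of 1.38 × 9/4 = 3.105. Their ratio is unchanged, so n stays at about 160. The pilot bands alone do not fix an SD. With children spread evenly within each band and percentages rescaled from 99%, the mean is (0.20 × 3.5 + 0.77 × 8) / 0.99 = 6.93 and the SD is 2.31. The narrowest arrangement (6 and 7 foods in the two upper bands) gives SD 1.04. The widest (1 and 9 foods) gives 3.37. At SD 2.31 before clustering, 160 per arm has 49% power for a 0.5-food gain and 99% for a 1.125-food gain: 1.125 / (2.31 × √(2/160)) − 1.960 = 2.40, and Φ(2.40) = 99%.

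**The case against.** The strongest defence has four parts.

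- **The trial aims for 400, not 320.** At ICC 0.01 that gives 90–91% without any adjustment. This stands. However, the protocol does not present the 400 as an allowance for clustering, and it warns that recruitment may be difficult.
- **Baseline adjustment is planned.** It could restore 90% in part of the assumed ICC range (Step 4). This also stands, though the sample size paragraph does not invoke it.
- **Classes are paired within schools.** In the protocol's example, both classes belong to one year group. If the analysis uses the pairing, some between-class variance is removed and the simple design effect may overstate the loss. Few clusters pull the other way. The documents do not allow either to be quantified.
- **The borrowed inputs are openly declared as imperfect.** That is fair for the inputs, but it does not justify a formula for a different design.

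Two stronger readings are tempting. A reader might infer that the trial lacks 90% power. Without an ICC or a baseline correlation, the documents do not show that; they show only that the claim is unsupported. A reader might also infer from the nine-food scale that power is far lower, for example 49%. That result changes the SD and keeps the four-food difference. The gloss of one more food favours an unscaled 0.5, but the SD remains unknown between about 1.0 and 3.4, so no direction is established.

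**Conclusion.** The point holds in this form: 160 per arm is the answer for individually randomised children, the trial randomises classes, and the stated 90% therefore does not follow. On the protocol's own difference and SD, any positive class ICC takes the stated calculation below 90%. The shortfall is a few percentage points at ICC 0.01 and about half the claimed power at 0.10.

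These sizes rest on an assumed ICC and class size, the normal approximation and no baseline adjustment. The planned analysis could do better through adjustment and pairing, or worse through few degrees of freedom.

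The mismatch of age, number of foods and Gusto weighting leaves the inputs unsupported, but does not show whether the required number is too small or too large. The omission of clustering carries the conclusion on its own.

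**What to change.** Replace the 90% sentence with the power, or the detectable difference, for about 400 children in the expected number of classes. State:

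- the expected number of classes and of consenting children per class;
- a range of class-level ICC and the resulting design effect;
- degrees of freedom based on clusters or pairs;
- a range of baseline–follow-up correlation, if adjustment is to be credited;
- the SD of the nine-food score, taken from the trial's own pilot;
- the target difference on the nine-food scale, saying whether it refers to the self-reported or the Gusto-weighted score.

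The cost is a recalculation and, probably, a less favourable stated power. No extra recruitment or change of design is needed. The pilot as described reports no repeat testing and no class-level results, so the ICC and the baseline correlation may have to be given as assumed ranges.

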### Recruitment {15}

Schools will be recruited by open invitation via social media, word-of-mouth, and through local authority school-facing teams and programmes. Schools will benefit from free teacher training and reimbursement of the financial cost of the produce used for the intervention. We appreciate that this process will likely over-sample schools with an interest in food and food education. By definition, this group is the most likely to implement food education interventions, and so study results should be broadly applicable to schools choosing to introduce sensory food education. However, the results of the study may not be so broadly applicable to schools mandated to introduce sensory food education.

### Assignment of interventions: allocation

#### Sequence generation {16a}

Sequence generation will be video recorded instantaneous randomisation (die roll).

#### Concealment mechanism {16b}

None, as we will use instantaneous randomisation.

#### Implementation {16c}

The lead researcher will enrol participants. The PI will generate the random sequence and assign clusters to the experimental/control groups on the basis of randomisation.

### Assignment of interventions: blinding

#### Who will be blinded {17a}

Data analysts/video coders will be blind to condition (control/intervention) and time point (pre- or post-intervention) of a given video and participant under analysis. Due to the experiential nature of the intervention, it is not possible to blind the study participants (children and teachers) to their condition (control/intervention). The lead researcher, who will conduct data collection, will be pragmatically blinded to which classes/clusters are in which condition. However, this blinding is imperfect due to contact between the lead researcher and participants during data collection (e.g. a child might talk about doing Flavour School activities, revealing that their class is in the intervention group).

#### Procedure for unblinding if needed {17b}

The lead researcher will be unblinded after the first stages of data analysis. Specifically, when all measures have been conducted, to include the WTT supervised self-report (assessed by the lead research from the children’s ’My Tasting Card’, see Fig. 2), and the independent observers have annotated the video data with their assessment of ‘Valence’ and ‘Gusto’. The project supervisor, [name], will hold the cluster condition allocations and will inform the lead researcher at the appropriate time.

**Fig. 2 Fig2:**
[figure not shown]
**a** Each child has a selection of FV in a compartmentalised tray. Children are free to taste (or not) any of the items, in any order. **b** Children record their tasting with an ‘emoji’ drawing to indicate like/neutral/dislike. Untasted items are left blank (e.g. blue circle). The testing table. Up to 4 chidlren participate together, each with their own tray of food samples. Located centrally on the table is a dedicated camera for each child

#### Data collection and management

Survey data will be collected from parents and teachers. A teacher survey (see Additional file 1: Appendix 3) will estimate teacher engagement and process adherence. The online Caregiver Consent form also contains an optional survey asking parents about their child's eating behaviours, using a subset of the Child’s Eating Behaviour Questionnaire.

#### Plans for assessment and collection of outcomes {18a}

Behavioural data collection is conducted through a tasting activity we call ‘Flavour Explorers’. The activity itself is individual, but is performed in a peer-group of three or four to enable conversation and make the scenario comfortable for the children participating. The children are supervised by the researcher(s). The children sit on cushions on the floor, around a small circular table.

Each child is provided a small tray with nine compartments, each containing one food sample. Each compartment/food sample is marked with a different colour dot sticker. Each child is also provided a ‘My Tasting Card’, with nine colour blobs matching the food samples/compartments. When a child tries a food, they use ‘emoji’ style drawings to note their liking for the food (sad face, neutral face, or happy face) on their Card. See Fig. 2. Children are given as much time as they need (within reason), and sessions typically last between 8 and 12 min.

The sample consist of seven vegetables (including a legume and a herb), and two fruits, and include both common/familiar and obscure/unfamiliar produce. Different food sample sets will be used for pre- and post-intervention testing, counterbalanced at random by school class group. See Additional file 1: Appendix 1 for more details.

Flavour Explorers sessions will be video recorded, with an individual video stream for each child. A dedicated Yi4k+ action camera for each child is located in the centre of the table. The My Tasting Cards provide the raw data for analysis of willingness-to-taste (WTT) and liking, whilst video/audio provides raw data for affect from facial expression, and verbal engagement (Fig. 3).

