### Primary measures

‘Curiosity and confidence’ are operationalised in terms of the following observable proxy behaviours.Willingness to taste novel and familiar vegetables, legumes and fruit (supervised self-report)Non-verbal ‘Enjoyment and Engagement’ (from observation of children’s facial expressions)Verbal engagement (child’s speaking time and sensory vocabulary during the activity)Normalised linear combination (mean) of 1, 2 and 3 as an overall measure of ‘curiosity and confidence’ in tasting

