### Verbal engagement

Each time step of the video footage is annotated using one of 2 categories/levels of verbal behaviour: 0 = not talking; 1 = talking. These scores will then be summed across time steps, and divided by number of timesteps, to give one number describing the proportion of speaking time across the session. See Additional file 1: Appendix 2 for more details of the video coding scheme.

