### Statistical methods

#### Statistical methods for primary and secondary outcomes {20a}

For each participant, pre/post-intervention difference will be calculated for each primary measure, plus the normalised sum of primary measures (to represent overall ‘curiosity and confidence’). Each set of data will be analysed using regression models with pre-post difference as the outcome. Secondary measures will be examined using the same methods as primary measures. The number of clusters is too small to analyse using a multi-level model, however school and class will be included as a covariate.

For each participant, data will be collected at baseline and follow-up. The main outcomes (dependent variables) will be individual scores in WTT, enjoyment/engagement (from facial expression), and verbal engagement at follow-up. The difference in scores between the intervention and the control group will be calculated for each of the primary measures, plus an overall score consisting of the sum of primary measures which represents overall curiosity and confidence. Each set of data will be analysed using two level regression models (where appropriate), to take into account the clustering of children within schools. The analysis will be adjusted for baseline scores.

The intervention should benefit those children most in need of support. To reflect this in our analysis, we will split the participants into three sub-groups according to their score on a given measure at baseline (low, mid, high). Each grouping will cover 1/3 of the range for that measure. It is important that any benefits be observed in the low and/or mid groups and not just be driven primarily by the high group. High scores are considered desirable in all measures.

The liking secondary measure will be examined using the same regression methods.

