#### Methods for additional analyses (e.g. subgroup analyses) {20b}

At the individual level, we will control for any effects of sex, age, and Pupil Premium^2^ eligibility. At the group level, we will control for any effects of school and school class group. Any group differences will be interpreted in the light of information about process adherence and teacher engagement, as reflected in the teacher survey (see Additional file 1: Appendix 3).

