### Data collection

Building on work with US pre-school children [32], the video recorded “Flavour Explorers” activity is designed to give us a much richer observational window on children’s tasting behaviour than simple willingness-to-taste measures. The activity typically lasts for about 10 min, during which time we continuously record video of each child individually. This allows us to observe behaviours like smiling, grimacing, laughing and talking over an extended period of tasting behaviour. Though the activity itself is individual (see the “Plans for assessment and collection of outcomes {18a}” section for more details), it is conducted in a small peer group (4 children) to enable conversation and to make the activity more comfortable and fun for the children. Doing the activity alone with a researcher/stranger might feel strange or intimidating, which in turn could impact on children’s behaviour.

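### Children are scored at shared tables of three or four, but the stated models stop at school and class, so standard errors are wrong if scores at a table are correlated

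*Protocol article*

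**What the plan says.** Under Plans for assessment and collection of outcomes {18a}, the tasting activity is "performed in a peer-group of three or four to enable conversation". The Discussion, under Data collection, gives the group size as four: "it is conducted in a small peer group (4 children) to enable conversation". The legend of Fig. 2 allows up to four children at a table, "each with their own tray of food samples".

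All the primary measures come from this session: willingness to taste, facial enjoyment and engagement, verbal engagement, and their combination. Under Verbal engagement, talking is scored per time step for each child, "to give one number describing the proportion of speaking time across the session".

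Statistical methods for primary and secondary outcomes {20a} describes two models. The first is a single-level regression: "The number of clusters is too small to analyse using a multi-level model, however school and class will be included as a covariate". The second reads: "Each set of data will be analysed using two level regression models (where appropriate), to take into account the clustering of children within schools". Methods for additional analyses {20b} adds: "At the group level, we will control for any effects of school and school class group". The list under Independent measures includes school and class but no table or session. Participant timeline {13} sets the randomised unit as the class, paired within school.

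**The concern.** Children are grouped so that they can talk, and talk is itself part of a primary measure. A lively or reluctant table could plausibly shift the tasting, expression and speech of everyone at it. Dependence of this kind sits below class and school, the lowest levels named in either model.

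Positive correlation at a table means each further child there adds less information than the model assumes. Standard errors are then too small and the type I error is too high. Turn-taking in speech could work the other way and make the standard errors for speaking time too large. Either way, the reported precision of the treatment effect would not be the true precision.

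**Working it through.** **Inputs.** From the protocol: three or four children per table; a sample size based on a difference of 0.5 foods, SD 1.38, 90% power and 160 per arm; a target of 400+ children, about 200 per arm. Assumed, because the protocol does not give them: table ICC of 0.1, 0.2 and 0.3; two-sided 5% tests.

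**The plan's own figure.** n per arm = 2 × (1.960 + 1.282)² × 1.38² / 0.5² = 160.1, or 161 rounded up. The stated 160 is reproduced with a design effect of 1, that is, with every child independent of the others at the table, in the class and in the school.

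**Table effect alone.** With m analysed children per table, design effect DE = 1 + (m − 1) × ICC. The true standard error is √DE times the one reported, and the actual type I error is 2 × (1 − Φ(1.96/√DE)).

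| m | ICC | DE | True SE larger by | Type I error | Power at 160 per arm | Power at 200 per arm |
|---|---|---|---|---|---|---|
| 3 | 0.1 | 1.2 | 10% | 7.4% | 0.84 | 0.91 |
| 3 | 0.2 | 1.4 | 18% | 9.8% | 0.78 | 0.87 |
| 3 | 0.3 | 1.6 | 26% | 12.1% | 0.73 | 0.82 |
| 4 | 0.1 | 1.3 | 14% | 8.6% | 0.81 | 0.89 |
| 4 | 0.2 | 1.6 | 26% | 12.1% | 0.73 | 0.82 |
| 4 | 0.3 | 1.9 | 38% | 15.5% | 0.65 | 0.75 |

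The power columns assume that the analysis allows correctly for the table.

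**Opposite sign.** At ICC −0.1 and m = 4, DE = 1 − 0.3 = 0.70 and the type I error is 1.9%, so the test is too cautious.

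**Do the stated models absorb it?** This was simulated under an assumed layout: 8 class pairs in 5 schools, 24 children per class, tables of four within class, 3,000 runs per setting, no treatment effect. Type I error:

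| Table ICC | School-adjusted regression | Class fixed effects, contrast of arms | Paired class means |
|---|---|---|---|
| 0 | 0.051 | 0.052 | 0.049 |
| 0.1 | 0.090 | 0.092 | 0.049 |
| 0.2 | 0.116 | 0.119 | 0.052 |
| 0.3 | 0.154 | 0.161 | 0.049 |

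Adjusting for school does not help, because the treatment contrast lies within schools. Class as a fixed covariate does not help either. Treatment is a linear combination of the class indicators (17 columns, rank 16), and a contrast of class effects judged against within-class residuals still ignores the table.

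**Together with a class effect.** With a class ICC of 0.02, the school-adjusted regression gives 0.106, 0.144, 0.172 and 0.203 at table ICC 0, 0.1, 0.2 and 0.3. The first figure has no table effect in it and matches the formula: DE = 1 + 23 × 0.02 = 1.46. Paired class means stay between 0.047 and 0.055 in every setting.

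**The case against.** The strongest objection is that this is not a separate fault in the treatment comparison. Classes are randomised, so if tables sit within classes, a sound class-level analysis already carries the table variation. That stands: the simulation shows it, and it is why the fix works at class level. A reader might infer that a table random effect is indispensable; it is not. But neither stated model is a sound class-level analysis, so the protection is not in the plan.

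A second objection is that {18a} calls the activity itself individual and gives the children's comfort as a further reason for grouping. That describes the task: each child has a tray, a card and a camera. It does not make the scores independent. Still, the protocol speaks of enabling conversation; that children change one another's scores is an inference.

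Third, only children with caregiver consent contribute data, so fewer may be analysed per table than sat there. This stands. With two, DE is 1.1, 1.2 and 1.3 at the three ICCs, and the type I error is 6.2%, 7.4% and 8.6%.

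Fourth, seating and session logs may be described in documents not shown, and the individual video streams may let table membership be reconstructed. This softens the point about recording. It does not touch the models, whose levels the protocol itself fixes.

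Two stronger readings are tempting. A reader might infer that tables mix classes, so that intervention children model tasting for controls during measurement. No text says so. Food sets are allocated by class, which makes single-class tables the natural reading, though it is not stated. A reader might also infer that speaking time is a zero-sum share of table talk, with an ICC as low as −1/3. It is each child's own proportion of time steps, so all can be silent or talk at once, and that bound does not describe it.

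**Conclusion.** The point holds conditionally: following the plan as written gives wrong standard errors for any non-zero correlation at the table. The documents do not show that the correlation exists, how large it is or which way it runs, so it cannot be said that the intervals are too narrow. Under the assumed positive ICCs of 0.1 to 0.3, the nominal 5% test runs at 7.4% to 12.1% with three analysed children per table and 8.6% to 15.5% with four, before any class effect.

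The larger fault is that {20a} has no sound error term for the randomised class. That fault is present even without tables, and correcting it removes the table problem from the treatment comparison, provided that each table holds one class. What then remains concerns child-level analyses, chiefly the exploratory correlation between liking and willingness to taste. The FaceReader comparison is little affected: software and coders score the same video, so shared table mood largely cancels.

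**What to change.** - In {18a}, state that each table holds children of one class only, and record a table or session identifier at baseline and at follow-up.
- In {20a}, replace the two model descriptions with one that takes the randomised class as the unit for the treatment effect. Suitable choices are paired, baseline-adjusted class means, or a random class effect with a small-sample correction. Either absorbs the table correlation when tables stay within class.
- For child-level analyses such as the liking and willingness-to-taste correlation, use standard errors clustered by table, or a random effect for the follow-up table where it can be estimated. Membership may change between sessions, hence the follow-up table.

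The cost is one extra logged field, a sentence on seating and a little more analysis work. No extra children or staff are needed. Intervals will probably be wider, since class-level inference rests on few units: 8 pairs, as in the simulated layout, leave 8 − 1 = 7 degrees of freedom for a paired test.
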